## Is cognitive behavioural therapy a good treatment for chronic fatigue syndrome?

### Summary:

The Norwegian Directorate of Health has requested documentation on treatment for chronic fatigue syndrome, CFS/ME. With this trial, The National Competence Centre for Complex Symptom Disorders (NKSL) wants to contribute to knowledge on whether cognitive behavioural therapy is good treatment for CFS/ME. Even though standard, individual CBT together with graded exercise therapy so far is the best documented treatment, there is no national or international consensus due to few randomised trials, varying quality and moderate evidence. Therefore, our goal is to test the effect of individual standard CBT, in a randomized, controlled 1-year follow-up trial. Our second goal will be to test the effect of a newly developed and shorter individual CBT (I-CBT). If the shorter therapy turns out to be as good as or better than standard CBT, the shorter therapy will be an equal and more cost-effective treatment. Patients with nonspecific fatigue will undergo a thorough, multidisciplinary assessment at the The Department for Pain and Complex Symptom Disorders (ASSL), St. Olav`s Hospital, to be diagnosed with CFS/ME or other fatigue conditions. Patients diagnosed with CFS/ME will be offered treatment in our trial with randomisation to either short I-CBT or standard individual cognitive behavioural therapy or a control group. Primary outcome measures are physical function, health related quality of life and fatigue. NKSL is a research group at ASSL, St. Olav`s Hospital that wants research to be the basis for the operation of its three outpatient clinics; the clinic for pain, the clinic for CFS/ME and the clinic for assessment to work related rehabilitation at Hysnes, Norway.

In our opinion, this study fits perfectly with the announcement:

**Clinical research. Transitional research:** The health care system needs evidence-based information on treatment for this patient group, that is whether cognitive behavioural therapy is effective. The results can also be transferred to patients with complex symptom disorders. **Interdisciplinarity:** The trial will engage a broad spectrum of professionals both scientifically speaking (the project group) and clinical (multidisciplinary assessment). There are also simultaneous investigative studies of the CFS/ME patients where researchers outside the project group are involved in Regional Ethics Comity (REK) approved projects. **Randomised controlled trial (RCT):** The project has a good and clear research method with, among other things, a randomised controlled design, a power calculation that takes into account drop-outs (large patient group) and intention-to-treat (ITT) analysis. **Biobank:** The trial involves storing blood samples from all the included participants in a biobank, which provides opportunities for subsequent trials.

**Feasibility:** The trial has already been going on for two and a half years and inclusion of patients is soon to be completed. The study protocol is registered in Clinicaltrials.gov and has already been referred to as an ongoing trial in a report from Norwegian Research Centre for Health Services. **Relevance for the Health Authority. The use of environment, regional cooperation and interaction:** Patients with fatigue are referred from the entire region of Mid-Norway, and cooperation on these patients is important to ensure good and relevant care. The project can, after completion, contribute to more knowledge on treatment both nationally and internationally. The research group behind the application is an interdisciplinary environment that supports each other and works actively to raise competence in areas that are characterized by weaker research. The research environment represents several institutes at NTNU and cooperates with universities both nationally and internationally. The Norwegian Directorate of Health has in a letter to the Department for Health and Care requested more documentation on treatment for CFS/ME.

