There is no national or international consensus on treatment for chronic fatigue syndrome. Systematic reviews and randomised controlled trials have investigated the effect of several treatments for CFS/ME (10,11,12). CBT and grade exercise therapy (GET) are the only treatments that seems to be favorable (12,13). Even though most of these studies conclude that cognitive behavioral therapy (CBT) increases health related quality of life (HR-QoL) and physical function, fatigue and psychological comorbidity, no treatment has shown high evidence or a curative effect. Objections to CBT for CFS/ME have been targeting decreasing effect at follow up measures, the low number of studies and that evidence is regarded to be “moderate” independent of the outcome measures used (10). A few studies have reported that CBT causes harm or has no effect (14,15). Patient organizations have also been sceptic to CBT and grade exercise therapy, and some self-reported surveys initiated by patient organizations have concluded that CBT is a bad treatment for CFS/ME (16). Thus, they have recommended rest and pacing, but no systematic reviews support this recommendation. There has been a lot of turmoil, especially patients’ organizations, regarding the use of CBT. An evaluation of the treatment effect of CBT can give important information to patients and their next of kin and may correct undocumented patient management. Some patients diagnosed with CFS/ME spend months and years in bed, because of following advice that rest is the way back to normal functioning.

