## Research questions and hypotheses

Our main research question is whether cognitive behavioural therapy, CBT, is effective treatment for CFS/ME, this can be divided into 2:

- 1) Does cognitive behavioural therapy improve physical function, fatigue and psychological issues in patients diagnosed with CFS/ME?
- 2) Is short cognitive behavioural therapy, I-CBT, equal to or better than standard, long CBT intervention in treatment of CFS/ME?

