## Hypothesis

(1) Standard CBT (CBT) and short CBT (I-CBT) are significantly better compared to the waiting list control group (WLC) in the primary outcome measure physical function in SF-36 and in the secondary outcome measures fatigue and the rest of the SF-36 subdimensions.

(2) There is no difference in effect between I-CBT and standard CBT in the primary outcome measure physical function in SF-36 and in the secondary outcome measures fatigue and the rest of the SF-36 subdimensions.

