**Standardised CBT, long intervention:** The intervention consists of 16 weekly sessions plus a booster session four weeks after the 16th session, ad modum "Chalder/Kings College". The actual therapy manual is based on previous manuals from similar trials and associated with the fear avoidance theory (FA) of CFS. The FA theory focuses on the link between cognitive and behavioural responses. The following main elements are included in the intervention: (a) information and explanation of the CFS symptoms based on contemporary knowledge on both physical and psychological components, (b) agreement on goals for the

treatment (c) reading of self-help guides like *Coping with Chronic Fatigue* (d) avoidance of excessive activity or rest and/or sudden change in activity, (e) planning of regular, predictable, continuous activity to prohibit deconditioning, (f) recovering self-confidence and self-control by starting with a five- minute walk morning and night followed by gradual development (GET), and (g) classical CBT-procedures. A treatment manual for SCBT has been developed following [name] guidance. in use at the Division of CFS/ME, Kings College, UK (17). There will be regular supervision of the therapists in relation to this manual. All treatment sessions will be taped which will allow for quality control and satisfactory CBT guidance. Appropriate use of standard CBT will be quality assured using independent observers with CTACS quality assurance instrument afterwards (18) so that all therapists are quality assured as CBT therapists. Guidance is provided by a specialist in CBT guidance (psychiatrist, [name]) regularly once a month in a group, as well as individually when needed.

**Control group (WLC):** The control group is a waiting list control group in which the participants will be asked to wait for 16 weeks after primary assessment and randomisation before they are post-scored and then offered eight weeks of I-CBT outside the study. The ideal would have been a control period up to one year without intervention, but this will not possible due to ethical considerations.

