#### *Analyses:*

Calculation of sample size and power. We have calculated sample size assuming a mean change in SF-36 score of 10, 5, and 0 from baseline of respectively short I-CBT, standard CBT, and WLC group, a ‘within cell’ standard deviation (SD) on 15 and a correlation between baseline and post score on 0.3 (r-squared on 0.1). For a two-sided test with 5 % significance level and 80 % power, we calculated that we needed 40 patients in each group, 120 in total. Assuming a maximum drop-out level of 25 %, we calculated that we needed an additional number of 18 patients in each group, 174 patients in total. A mean change in SF-36 score of 10, 10, and 0 for short, standard, and WLC groups would increase power to 90 %.

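### The claim that short I-CBT is an equal, more cost-effective treatment is not made conditional on I-CBT beating the waiting list

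*Protocol*

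**What the plan says.** The Summary sets a second goal, to test the shorter therapy, and attaches a conditional conclusion about equality and cost-effectiveness: "If the shorter therapy turns out to be as good as or better than standard CBT, the shorter therapy will be an equal and more" … The condition names one comparison, I-CBT with standard CBT. It gives no test, margin or time point.

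Under Research questions and hypotheses, the second question is "Is short cognitive behavioural therapy, I-CBT, equal to or better than standard, long CBT intervention in treatment of CFS/ME". Under Hypothesis, two statements stand side by side. Hypothesis (1) says "Standard CBT (CBT) and short CBT (I-CBT) are significantly better compared to the waiting list control group (WLC") on SF-36 physical function. Hypothesis (2) says "There is no difference in effect between I-CBT and standard CBT in the primary outcome measure physical function in SF-36". Nothing makes (2), or the Summary's conclusion, depend on (1).

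Standard CBT is not presented as an established reference. The Background rates the evidence as moderate, cites a few studies reporting harm or no effect, and says "no treatment has shown high evidence or a curative effect". Whether CBT works is the first research question.

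Control patients are "asked to wait for 16 weeks after primary assessment and randomisation before they are post-scored" and are then offered I-CBT outside the study, so the 16-week post-score is the last comparison with untreated patients.

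**The concern.** Matching a reference therapy supports adopting the new one only if the reference works. Here that is an open question of the same trial. As written, the condition can be met when both therapies do nothing. It can also be met when standard CBT helps a little and I-CBT does not help at all, because the trial is too small to detect the gap reliably.

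The conclusion bears on practice: a shorter therapy offered as equal and cheaper, with results intended for primary care. Adding a non-inferiority margin would not be enough, since two equally ineffective therapies can also pass a non-inferiority test. The waiting-list arm can rule this out at 16 weeks, but the stated conclusion does not call on it.

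**Working it through.** **Inputs** (protocol, Analyses): mean changes 10, 5 and 0 for I-CBT, standard CBT and waiting list; SD 15; baseline correlation 0.3 (r-squared given as 0.1); "For a two-sided test with 5 % significance level and 80 % power"; 40 per group, raised to 58 for up to 25% drop-out. Triples below are true gains in the order I-CBT/standard CBT/waiting list.

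**The plan's own figure.** Residual SD after baseline adjustment: 15 × √(1 − 0.3²) = 14.31. For the overall three-group F test:
- 10/5/0: noncentrality = 40 × (25 + 0 + 25) / 14.31² = 9.77, power 0.795 (0.800 with r-squared 0.1).
- 10/10/0: noncentrality 13.02, power 0.901.

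The stated 80% and 90% are reproduced. They belong to an overall three-group comparison, not to the I-CBT versus standard CBT contrast.

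**Standard error of a pairwise difference at n = 40.** 14.31 × √(2/40) = 3.20; critical t on 116 df = 1.98.

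**Neither therapy works (0/0/0).** How often the condition is met depends on the reading:

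| Reading of as good as or better | Condition met |
|---|---|
| Not significantly worse, two-sided 5% | 1 − 0.05/2 = 97.5% (any n) |
| No significant difference | 1 − 0.05 = 95% |
| Point estimate at least equal | 50% |
| Lower 95% CI limit above −5 (assumed margin) | Φ(5/3.20 − 1.98) ≈ 34% |
| Lower 95% CI limit above −10 (assumed margin) | Φ(10/3.20 − 1.98) ≈ 87% |

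**Standard CBT gains 5 points, I-CBT none (0/5/0).** Not significantly worse: Φ(1.98 − 5/3.20) ≈ 66%. With a 5-point margin the true deficit sits on the margin, so non-inferiority is declared in about 2.5%. With a 10-point margin it is Φ((10 − 5)/3.20 − 1.98) ≈ 34%.

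**With the gate** (I-CBT significantly better than waiting list, right direction), combined with the not-significantly-worse reading, by simulation at n = 40:
- 0/0/0: 2.5%.
- 0/5/0: 2.4%.

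In both cases I-CBT truly equals waiting, so the gate alone caps the rate at 2.5%, whatever reading is used for the second step.

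**Cost of the gate when I-CBT truly gains 10 points.**
- n = 40: pass rate Φ(10/3.20 − 1.98) ≈ 87%, so missed in about 13%.
- After drop-out: 58 × 0.75 = 43.5 per group. At 43 the SE is 14.31 × √(2/43) = 3.09, pass rate about 90%, so missed in about 10%.

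**The case against.** The strongest reply is that the waiting list is already used. Hypothesis (1) requires both therapies to beat it on the primary outcome, the Intervention section compares both with it, and the sample size is for three groups. If both therapies failed, the same trial would report hypothesis (1) as failed. This stands: a reader might infer that the protocol ignores the waiting list, and the documents do not support that. Only the link between hypothesis (1) and the conclusion is missing.

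It can also be said that the Summary sentence states an aim and is not an operational rule, and that 97.5% is simply one minus half of alpha for any two arms with equal means. Both points are fair. The figure belongs to an assumed reading and should not be quoted without it.

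Further, when neither therapy works the two really are equal, so the word equal is not false. What lacks support is the claim of a useful, more cost-effective treatment. In the 0/5/0 case equality is false, but much of that fault lies in the missing margin: a 5-point margin alone would bring it to about 2.5%, a 10-point margin would not.

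Finally, test order is often left to a statistical analysis plan, which is not at hand. That would answer a complaint about a missing detail. It does not answer this one, because the protocol itself states the conclusion and its condition.

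**Conclusion.** The point holds in a limited form. The conclusion about I-CBT and hypothesis (2) are not conditional on I-CBT beating the waiting list, in a protocol that treats the reference therapy as unproven.

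The rates of 97.5% (0/0/0) and about 66% (0/5/0, n = 40) rest on the planning SD and correlation, and on reading as good as or better as not significantly worse. The other 0/0/0 readings range from about 34% to 95%, all far above 2.5%. A reader might infer that the trial would make a false equality claim 97% of the time. The documents do not support that: no test is fixed, and with no effect in any arm the equality is true.

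This is a correction to the wording of the conclusion and its condition. It does not invalidate the design, which already contains the comparison needed.

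**What to change.** State in the Summary and in hypothesis (2) that equality or cost-effectiveness of I-CBT will be claimed only if, in this order:

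1. I-CBT is significantly better than the waiting list on SF-36 physical function at the 16-week post-score; and
2. I-CBT then meets the criterion against standard CBT, judged by the 95% CI against a pre-stated margin and at a named time point, not by a non-significant difference.

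If step 1 or step 2 fails, report the I-CBT versus standard CBT difference with its 95% CI and make no such claim.

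This needs no new patients, visits or data. Testing the two steps in fixed order needs no alpha adjustment within that sequence. Standard CBT versus waiting list, the first goal, lies outside it and needs its own place in the testing plan.

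The cost is power. If I-CBT truly gains 10 points, step 1 is missed in about 13% of trials at 40 per group, and about 10% at the 43 to 44 left after 25% drop-out from 58. Step 2 costs more: when the therapies are equal it succeeds in about 34% of trials with a 5-point margin and 87% with a 10-point margin at n = 40. The full claim cannot succeed more often than the weaker step, so the margin should be chosen with that in view. Requiring both therapies to beat the waiting list would be stricter. Under the plan's 10/5/0 assumption that requirement, combined with the not-significantly-worse reading, is met in only about 33% of trials at n = 40, so gating on I-CBT alone is the more workable choice.

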## **Background for this project**

Chronic fatigue syndrome (CFS/ME) is characterized by disabling fatigue that exceeds a period of 6 months and which inhibits the individual from daily life's functions without an ongoing strain that can explain the ailments. Additional symptoms include impaired memory, impaired concentration, sore throat, muscle and joint pain, headache, sleep disturbances, and pathologically prolonged symptomatology following stress. The diagnosis criteria for CFS/ME requires that the fatigue must be medically unexplained, newly emerged and with little effect of rest, but usually occurs after physical and mental stress. Some people may be hypersensitive to light, sound and touch, as well as developing irregularities in the autonomic nervous system (1,2). The diagnosis is made based on diagnostic criteria in which specific diagnoses that can cause chronic fatigue should be excluded. The aetiology and pathogenesis of CFS is largely unknown and so far, no consensus has been reached (2,3), but there is a common opinion that the causes of this illness are complex (4).

Epidemiological studies have shown that up to 30% of populations have unspecific, chronic fatigue lasting for more than six months at any given time. According to a report from the Norwegian Research Centre for Health Services (5), there are an estimated 10 to 20,000 inhabitants in Norway who have been diagnosed with chronic fatigue syndrome, and thus a population prevalence of 0.2 to 0.4%. CFS/ME patients frequently see a doctor, averaging 13 consultations per year in the general medical services and 5 consultations per year in secondary care (6). The Norwegian Directorate of Health assumes that fatigue patients have frequent contact with the primary health care in Norway. Approximately half of the patients are expected to get sufficient help in the limits of what can be offered in primary health care, while the rest need additional help (7). Age varies between 40-59 years, and there are more women than men, approximately 3:1 (8,9).

There is no national or international consensus on treatment for chronic fatigue syndrome. Systematic reviews and randomised controlled trials have investigated the effect of several treatments for CFS/ME (10,11,12). CBT and grade exercise therapy (GET) are the only treatments that seems to be favorable (12,13). Even though most of these studies conclude that cognitive behavioral therapy (CBT) increases health related quality of life (HR-QoL) and physical function, fatigue and psychological comorbidity, no treatment has shown high evidence or a curative effect. Objections to CBT for CFS/ME have been targeting decreasing effect at follow up measures, the low number of studies and that evidence is regarded to be “moderate” independent of the outcome measures used (10). A few studies have reported that CBT causes harm or has no effect (14,15). Patient organizations have also been sceptic to CBT and grade exercise therapy, and some self-reported surveys initiated by patient organizations have concluded that CBT is a bad treatment for CFS/ME (16). Thus, they have recommended rest and pacing, but no systematic reviews support this recommendation. There has been a lot of turmoil, especially patients’ organizations, regarding the use of CBT. An evaluation of the treatment effect of CBT can give important information to patients and their next of kin and may correct undocumented patient management. Some patients diagnosed with CFS/ME spend months and years in bed, because of following advice that rest is the way back to normal functioning.

The Department for Pain and Complex Symptom Disorders (ASSL), CFS/ME outpatient clinic, St. Olav’s Hospital, has since 2008 received patients with fatigue for inclusion in a consecutive, randomised, controlled treatment trial with short and long/standard individual cognitive behavioural therapy as intervention. Thus, we will use the collected data from ASSL, and plan to have enough patients included per 01.01.2012 according to conducted power calculation. The study protocol is approved by the Regional Ethics Comity (REK), project number 4.2008.2586, and is also registered in Clinical trials.gov. The trial is also referred to in a report from the Norwegian Research Centre for Health Services (5). The Norwegian Directorate of Health has referred to this report in a letter to the Department for Health and Care which has requested more documentation on treatment for chronic fatigue syndrome, CFS/ME. Our project has started without research funding as an outpatient offer to this group of patients. The collection of data will soon be completed, and everything is now ready for a PhD candidate to start working on the material.

### **A short description of the research environment**

This project is run by The National Competence Centre for Complex Symptom Disorders (NKSL). Leader of this research group is professor [name], has gathered competence and resourceful people around the research group which celebrated a ten-year anniversary this year. NKSL, which is subject to St. Olav’s Hospital HF, consists of several part-time employed scientists and professors (see Appendix). The aim of NKSL is to develop guidelines, treatment measures and procedures of cooperation

to avoid that people who are at risk of developing complex symptom disorders develops chronic illness and becomes disabled. The foundation of the research group is built on the biopsychosocial model, with focus on understanding illness and symptoms as a combination of biological, mental and social factors. NKSL has worked for national competence development by arranging classes and seminars for all relevant professions in the health care system. Developing a national Norwegian education for specialist nurses in pain medicine in cooperation with HIST (local nursing school) at the value of 15 student credits is an example of this work by NKSL. This cooperation between NKSL and HIST has now successfully been going on for three years. Scientist connected to NKSL have so far in 2011 and during the entire year of 2010 published 22 and 27 PubMed-registered articles respectively. Meetings to discuss articles and the ongoing work of our PhD-candidates are arranged weekly, and a 2-day long research seminar was recently arranged in the occasion of NKSL's anniversary. A 2-day gathering for PhD-candidates in February 2012 is also planned. It important to emphasize that NKSL as a National Competence Centre does not receive funding for research, and thus has to apply for funds to be able to start research projects. This project is a part of NKSL's aim, via clinical close to patient research, to describe, understand and find evidence-based treatment approaches for patients with chronic fatigue syndrome. Experience from handling other complex symptom disorders implies that we also aim for interaction with the primary health service in this project. Our aim is to provide evidence-based advice back to the primary health service within a previously rather weak area of research.

